# Comparing the effectiveness of the BPMAP (Blood Pressure Management Application) and usual care in self-management of primary hypertension and adherence to treatment in patients aged 30–60 years: study protocol for a randomized controlled trial

**DOI:** 10.1186/s13063-016-1638-0

**Published:** 2016-10-21

**Keywords:** Hypertension, m-Health, Self-management, Adherence to treatment

## Abstract

**Background:**

Hypertension is one of the most important and well-known risk factors for cardiovascular diseases. Unfortunately, in spite of effective treatments, adherence to the regular use of drugs and other nondrug treatments, such as lifestyle improvement, is often poor. This study evaluates the effectiveness of an educational, supportive intervention – in the form of a Blood Pressure Management Application (BPMAP) – on self-management in patients with primary hypertension on controlling the determinant factors of hypertension, and on adherence to treatment.

**Methods/design:**

A two-arm, parallel-design randomized controlled clinical trial will be conducted on 30 to 60 year-old patients with primary hypertension who are attending the Tehran Heart Center. One hundred and thirty-two (132) patients will be randomly assigned to the intervention and control (usual method) groups. The most important inclusion criteria are, having primary hypertension and being pharmacologically treated for it, and not having developed the complications of hypertension, such as myocardial infarction, cerebral stroke and cardiac insufficiency. The participants should be able to read Persian and be able to use the application.

The most important outcomes of the study include adherence to treatment, weight control, and regular monitoring of blood pressure which are assessed in the primary assessment (baseline data questionnaire) and again at the 8^th^ and 24^th^ weeks. The intervention is a mobile application that has capabilities such as reminders and scientific and supportive information.

**Discussion:**

This application has been programmed to reduce many of the nonadherence factors of hypertension treatment. Therefore, the findings may contribute to a rise in adherence to treatment. If proven to have an appropriate impact, it may be extended for use in the national hypertension control plan.

**Trial registration:**

This study was registered in the Iran Randomized Clinical Trial Center under the number IRCT2015111712211N2 on 1 January 2016.

**Electronic supplementary material:**

The online version of this article (doi:10.1186/s13063-016-1638-0) contains supplementary material, which is available to authorized users.

## Background

Cardiovascular diseases (CVD) are the primary worldwide cause of morbidity and mortality. The death rate caused by CVD is expected to reach 23.6 million by 2030 [1]. Hypertension (HTN) is second only to obesity in its contribution to the etiology of CVD. With every 10 mmHg elevation in blood pressure (BP), the risk of CVD increases by 30 % [2]. Adherence to drugs, weight loss, smoking cessation, the Dietary Approaches to Stop Hypertension (DASH) diet plan and a low-salt diet, and taking appropriate exercise – particularly aerobic – are among the most important factors of disease control [2]. In spite of effective medical treatments for HTN, patients’ level of adherence to regular drug use has been reported at only 30–50 % at the international level [3].

Some of the reasons for nonadherence to treatment are: the drugs’ side effects; the patient’s disbelief in the efficacy and benefit of therapy; lack of motivation; the absence of bothersome physical symptoms in some patients; lack of knowledge and appropriate behavior toward drug therapy and dietary regimens; miscommunication between the patient and physician; the complexity of therapy; inadequate attendance for follow-up on the part of the patient, and certain psychological issues such as depression [2, 4].

The widespread use of smart phones enables their use – in the form of mobile applications – for beneficial medical and health-related purposes [5]. Nowadays, clinical applications can be used in smart phones as they have the following capabilities; audio-visual communication, Short Message Service (SMS), multimedia, medical sensors, the ability to connect to various devices for registering vital signs, such as electrocardiographic (ECG) monitoring, BP monitoring, the automatic transfer of data to registry systems, and the ability to connect to the Internet [6, 7]. Many studies have examined the effectiveness of mobile applications, most of which have reported positive results [1, 7].

As mentioned earlier, adherence to treatment is not favorable in spite of effective therapies. Here, we intend to evaluate the impact of an intervention aimed at overcoming the many barriers of adherence in HTN. The intervention has been designed in the form of the Blood Pressure Management Application (BPMAP) software application to enhance self-management in the control of the disease and to improve adherence in patients with primary HTN.

## Methods/design

### Overview

The main goal of this study is to evaluate the effect of the BPMAP mobile application on self-management in hypertensive patients. The application has been programmed to enhance individuals’ knowledge of the disease, its subsequent problems and methods of control, regular use of drugs, observance of the low-sodium and DASH diets, level of physical activity, smoking cessation, and weight loss. The assumption here is that this application can enable individuals to better control the determinant factors of HTN and reduce the possibility of its complications.

### Study design

This study is a randomized controlled, parallel-design clinical trial intended to demonstrate the impact of 6 months’ use of the BPMAP application on self-management in hypertensive patients, on their adherence to treatment, and the control of their risk factors for HTN.

The protocol is guided by the Standard Protocol Items: Recommendations for Interventional Trials (SPIRIT) 2013 Statement (see Additional file 1).

### Study setting

The participants will be selected from the patients attending the Tehran Heart Center Clinic. The Tehran Heart Center is a tertiary-care, educational subspecialty center for CVD affiliated with Tehran University of Medical Sciences. It has 460 beds and is one of the most well- equipped, specialized care centers for CVD in the region. Annually, an average 113,316 outpatients, 23,879 inpatients and 4331 open-heart surgery candidates are treated at the center [8].

The outcomes of the study (adherence to treatment, weight loss, regular BP monitoring) will be evaluated at the primary assessment (baseline data questionnaire) and again at the 8^th^ and 24^th^ weeks (Fig. 1).

**Fig. 1 Fig1:**
[figure not shown]
The procedure of the study evaluating the impact of the Blood Pressure Management Application (BPMAP)

## Intervention

### Intervention and control groups

In addition to the usual care, the participants of the intervention group will receive the educational, supportive mobile application-based intervention (Additional file 2). The participants will have these applications for 6 months and the aforementioned measurements will be registered in it. Reminders for dose and time of drug intake, date of clinical visit, and other reminders will be activated. The users will be provided with the scientific information and skills required to identify the disease and its methods of control by the mobile application.

The participants in the comparison arm will receive the usual standard care based on the Joint National Committee (JNC) guideline. The usual care includes, measuring the patient’s BP, necessary assessments based on the patient’s history and circumstances, the specialist physician’s judgment, medication prescription, and other medical measures. The number of appointments and assessments in each group will be the same. The intervention and control participants’ appointment days will differ and the members of one group will not be in touch with those of the other.

The BPMAP application contains educational content that is meant to raise the level of knowledge in hypertensive patients regarding its complications and methods of control. Moreover, it contains supportive measures such as important reminders for time of drug use, smoking cessation, and weight loss.

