#### Regular BP monitoring

BP can be regularly monitored by regularly measuring and saving the relevant data in the mobile app. For every timely registration a score will be awarded. This part of the study is 60 days long. The participants will be asked to measure and register their BP once every other day. A score of 25 and higher will be considered appropriate.

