### Follow-up

The participants will be examined seven times at 2-week intervals (Table 1). In the first visit, after ensuring the participant’s inclination to participate in the study and after the informed consent form is completed, the baseline data questionnaire will be completed by the researcher. Clinical measurements, such as systolic and diastolic BP, waist circumference and hip circumference, BMI, and biochemical measurements, such as LDL, HDL, and total cholesterol levels, will be performed.

**Table 1 Tab1:** Steps taken in each visit

	Study period										
	Enrollment	Allocation	Post allocation								Close-out
Week	−1 to 0	0 ± 2 days	2 ± 2 days	4 ± 2 days	6 ± 2 days	8 ± 2 days					24 ± 2 days
Time point	1^st^ visit	2^nd^ visit	3^rd^ visit	4^th^ visit	5^th^ visit	6^th^ visit					7^th^ visit
Enrollment:	×										
Eligibility screen	×										
Informed consent	×										
Allocation	×										
Intervention		×	×	×	×	×	×	×	×	×	×
Assessment	×					×					×
Baseline variables	×					×					×
Measuring adherence to treatment	×					×					×
Measuring adherence to the diet	×					×					×
Evaluating the predisposing, enabling, and reinforcing factors of adherence	×					×					×
Measurement of systolic and diastolic BP, waist circumference, and BMI	×	×	×	×	×	×	×	×	×	×	×
Evaluating the regular monitoring of BP by the mobile application	×	×	×	×	×	×	×	×	×	×	×
Evaluating the usability of the software						×					×
Evaluating the level of satisfaction of the software/application						×					×

*BMI* Body Mass Index, *BP* blood pressure

The 2nd visit will be made a week after the first. The application will be installed on the cell phones of the intervention group’s patients and its operation will be taught to them. Any problems that arise will be dealt with accordingly. Moreover, the sphygmomanometer used by the patient at home will be evaluated for its precision and sensitivity (calibration). In order to ensure that the patients measure their BP correctly at home, the methods applied by them will be controlled, and if faulty, corrected. Clinical measurements and usual care will be performed. The usual care includes history taking, BP measurement, and diagnostic and therapeutic measures based on the JNC guideline on high blood pressure.

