From the 2nd visit onward (up to the 6th visit) patients will be visited every 2 weeks. In each visit the patient’s BP, weight and waist circumference will be measured, and standard antihypertensive therapeutic measures – based on the JNC guideline – will be taken.

On the 6th visit, in addition to the assessments made throughout the 2^nd^ to 5^th^ visits, the baseline data questionnaire will be completed for the patients as well.

On the 7th visit, which will be conducted 16 weeks after the 6^th^ visit, the baseline data questionnaire as well as clinical assessments will be evaluated.

On the 6th and 7th visits, the intervention group’s patients will be asked whether they are familiar with another person involved in this study. If the response is positive they will be asked further questions and the data will be included in the analysis. This question will be included to take into account the possibility of contact between the participants of the control and intervention groups.

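### Visit-date reminders are described only for the app arm and two consecutive missed visits end participation, so follow-up may differ by arm, in a direction the documents do not settle

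*Protocol article*

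**What the plan says.** All references are to the protocol article.

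- **Who has the app.** Under Intervention and control groups, on top of usual care, "the participants of the intervention group will receive the educational, supportive mobile application-based intervention". For the other arm: "The participants in the comparison arm will receive the usual standard care based on the Joint National Committee (JNC) guideline". The description of usual care that follows mentions no appointment reminder.
- **What the app prompts.** The same section says: "Reminders for dose and time of drug intake, date of clinical visit, and other reminders will be activated".
- **Same visits for care and measurement.** Under Follow-up, for visit 2: "Clinical measurements and usual care will be performed". Study setting says that the outcomes "will be evaluated at the primary assessment (baseline data questionnaire) and again at the 8^th^ and 24^th^ weeks". Follow-up places the repeat questionnaire at visits 6 and 7. There is a long gap between them: "On the 7th visit, which will be conducted 16 weeks after the 6^th^ visit".
- **Same schedule in both arms.** "The number of appointments and assessments in each group will be the same".
- **Exclusion.** Withdrawal criteria lists events that exclude a participant from the study. Two matter here: failing to attend two visits in a row, and going more than a week without registering data in the app.
- **Analysis.** Statistical methods names intention-to-treat as the main approach, then says that the final results are analysed per protocol. Lost data are to be multiply imputed.

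**The concern.** The article equalises the number of appointments but not, as far as it says, the prompting to keep them. The arm that is prompted is the intervention arm, and the visits in question are those at which the questionnaire and clinical outcomes are taken. Nonattendance then ends participation.

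Attendance is unlikely to be unrelated to the outcome. Background and Discussion both list poor follow-up attendance among the reasons for nonadherence. If fewer controls attend, and the absent controls are poorer adherers, the controls who remain look better than the arm as randomised.

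The rule also discards data that could be had. Visits 3 and 4 fall at weeks 2 and 4 and carry no adherence questionnaire in Table 1. A patient who misses both is excluded before either post-baseline questionnaire is due. Under intention-to-treat that patient should stay in the study and be assessed at weeks 8 and 24.

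**Working it through.** **The plan's own figure.** The article gives no attendance or dropout rate by arm. Its only allowance is 10% overall under Sample size: 120 × 1.10 = 132, or 66 per arm. That is 6 patients per arm above the required 60. All rates below are assumptions, for illustration only.

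**Missed-visit rule.** Let m be the chance of missing any one visit, with misses independent. Let a(n) be the chance of getting through n visits without two consecutive misses:

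a(0) = a(1) = 1; a(n) = (1 − m) × a(n−1) + m × (1 − m) × a(n−2)

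- m = 0.20: a(2) = 0.960, a(3) = 0.928, a(4) = 0.896, a(5) = 0.865, a(6) = 0.836. Over the six visits 2 to 7, the share excluded is 1 − 0.836 = 16.4%.
- m = 0.10: a(2) = 0.990, a(3) = 0.981, a(4) = 0.972, a(5) = 0.963, a(6) = 0.954. The share excluded is 4.6%.
- At m = 0.05 the share is 1.2%, and at m = 0.30 it is 32.7%.

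If reminders halved the miss rate from 20% to 10%, this rule alone would exclude 66 × 0.164 = 10.8 controls and 66 × 0.046 = 3.0 app patients. The app is installed at visit 2, so its reminder cannot act before then. Counting only visits 3 to 7, the shares are 1 − a(5) = 13.5% and 3.7%, and the contrast remains.

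**App-lapse rule.** It can apply only to app users. Take the registration schedule under Regular BP monitoring, "The participants will be asked to measure and register their BP once every other day", which gives 60/2 = 30 entries over the 60 days of that part of the study. Read more than a week without registration as four consecutive missed entries. The app-arm share excluded is then:

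| Chance of missing one entry | Excluded within 60 days | Excluded within 24 weeks, if the schedule ran on |
|---|---|---|
| 20% | 3.4% | 9.9% |
| 30% | 14.7% | 37.7% |
| 40% | 36.6% | 74.0% |

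No control is excluded by this rule. Under these assumptions app-arm exclusions can fall well below the control figure of 16.4% or well above it.

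**Effect on the comparison.** In an analysis of those who remain, suppose a share d is lost from an arm and the tendency to be lost has correlation r with low adherence. The mean of those remaining rises by r × SD × φ(z_d)/(1 − d), where z_d is the d-quantile of the standard normal. The SD of 10 and the true difference of 5 come from Sample size. At r = 1 the rises are:

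- d = 5%: 1.09
- d = 10%: 1.95
- d = 20%: 3.50
- d = 30%: 4.97

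Two chosen scenarios, with r from 0.3 to 1.0:

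- Controls lose 20%, app arm 5%: at r = 1, 5 + 1.09 − 3.50 = 2.6; at r = 0.3, 5 + 0.33 − 1.05 = 4.3. The app's effect is understated.
- Controls lose 10%, app arm 30%: at r = 1, 5 + 4.97 − 1.95 = 8.0; at r = 0.3, 5 + 1.49 − 0.58 = 5.9. The effect is overstated.

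The same true difference can therefore appear too small or too large, depending on which rule removes more patients.

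**The case against.** The strongest case against the point has four parts.

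- **The direction is not given.** A reader might infer from the reminder and the missed-visit rule that outcome data will be more complete in the app arm and that the app's benefit will be understated. The documents do not support that. The app-lapse criterion stands on the same list, touches only app users and removes the least engaged of them. A reader might also put the understatement at 0.5 to 1.0 point, taking 20% against 10% missing and a gap of 5 to 10 points: (0.20 − 0.10) × 5 = 0.5 and (0.20 − 0.10) × 10 = 1.0. Every input there is assumed, and app-lapse exclusions are left out. This objection stands in full.
- **Silence about controls is not evidence.** The article does not say that controls receive no reminder, and clinic booking practice is detail that a condensed article may omit. This stands, and the reminder part of the fix is conditional for that reason. The exclusion rule does not depend on it.
- **The reminder is part of the intervention.** The comparison is app plus usual care against usual care, so prompting controls alters the comparator. This is fair for clinical attendance. It does not justify letting attendance decide whether outcomes are collected.
- **The analysis already protects.** Intention-to-treat, baseline adjustment and multiple imputation are all stated, and imputation can recover what baseline and earlier visits predict. It cannot recover the part driven by later, unobserved adherence. Excluding patients from the study, together with the sentence on per-protocol final results, weakens the protection.

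Nor do the visits capture every outcome: regular BP monitoring is registered in the app. The point is limited to the questionnaire and clinical measurements.

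**Conclusion.** The point holds as a risk of differential follow-up, with net direction and size unknown. The text supports three facts: visit-date reminders are described only for the app arm, the questionnaire and clinical outcomes are taken at those visits, and two consecutive missed visits exclude a patient whose week-8 and week-24 data may still be obtainable. That exclusion conflicts with intention-to-treat whether or not controls are reminded in some other way.

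The figures of about 16% and 5% rest on assumed miss rates of 20% and 10% and on independent misses. They show that the rule could matter against a 10% overall loss allowance; they do not predict attendance. That the excluded controls would be the poorest adherers is plausible and fits the article's own account of nonadherence, but it is not established.

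**What to change.** 1. In Withdrawal criteria, stop using nonattendance at two consecutive visits as a reason for exclusion from follow-up and analysis.
2. Treat a lapse in app registration the same way: record it as non-adherence to the intervention, not as a reason to leave the study. Changing only the missed-visit rule would leave in place the one exclusion that is arm-specific on its face.
3. Invite every randomised patient to the week-8 and week-24 assessments, whatever visits were missed before, and analyse all as randomised.
4. Report attendance and missing outcomes by arm.
5. If controls are not already reminded, send both arms the same study reminder, by the same route and with the same lead time, for visits 6 and 7. If they are, one sentence in the article settles the matter.

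The cost is a change of wording, continued invitations to patients who have missed visits, and at most two messages per participant. The downside of the common reminder is that control attendance at the two outcome visits would be slightly better than in unprompted care. It also does not fully equalise prompting, because the app's own reminder stays active, so items 1 to 4 matter more. Trial status gives the trial as recruiting, so the changes can still be adopted.

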### Intervention delivery

The software will be installed on the mobile phone and its operation will be taught individually. The patients will work with the application in the presence of the research team, and any existing problems will be resolved. Since BP measurement will take place at the individual’s home and with a personal sphygmomanometer, the patients’ personal sphygmomanometers will be calibrated at the same time that the application is installed. In case there is a large difference in readings, or if the sphygmomanometer is faulty, the patient will be advised to change it. The strategies foreseen for adherence improvement include reminders set at defined intervals in the form of pop-up messages. In order to monitor adherence, the data collected on the server will be used.

In addition to the application, a server has been designed in which the users’ activities will be collected. Items such as the duration the application has been left open by the user, the sections used by the user (in addition to registering their time and duration), and BP registration, etc. will be registered. Every time the user’s mobile is connected to the Internet, the data will be uploaded and saved on to the server. These data can be used as a proxy of adherence to the intervention.

## Outcomes

### Primary outcomes/clinical

The preintervention clinical measurements will be taken at weeks 8 and 24. These measurements include: systolic and diastolic BP, total cholesterol level, high-density lipoprotein (HDL) level, low-density lipoprotein (LDL) level, Body Mass Index (BMI), and waist circumference.

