### Primary outcomes/behavioral

Assessment of health behaviors affecting hypertension, such as healthy diet, physical activity level, checking and monitoring BP, adherence to treatment, and predisposing factors, enabling factors and reinforcing factors contributing to adherence to treatment, and smoking cessation.

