#### Adherence to antihypertensive medication use

This will be assessed with the Hill-Bone High Blood Pressure Therapy Compliance Scale, which includes 14 items, at the initial and final assessments [9–11]. Individuals will score from 14 to 56. An increase exceeding 20 % of the Compliance Scale score is considered effective.

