## Outcome measures

The primary outcomes of the intervention will be measured by, the researcher-made questionnaire, a manual sphygmomanometer, a weighing scale, a measuring tape, and biological tests.

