## Statistical methods

The qualitative findings of the study will be described using frequency and percentage frequency, and the quantitative findings will be described using mean and standard deviation. To analyze the effectiveness of the main outcome variable of the study, we will use analysis of covariance (comparison of mean changes in score of the adjusted questionnaire – based on the baseline score at the beginning of the study and other possible confounding factors) at a confidence interval of 95 %. This approach will be repeated for all the quantitative variables.

The remaining qualitative variables of the study will be compared by the chi-squared test between the two groups. The main approach of the study will be intention-to-treat. The final results will be analyzed per protocol. Lost data will be replaced through multiple imputation techniques.

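### Thirteen to fifteen outcomes are labelled primary and none secondary, although the trial is sized on the Hill-Bone score alone and the analysis section speaks of a single main outcome variable

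*Protocol article*

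**What the plan says.** **Labels.** The section Primary outcomes/clinical lists "systolic and diastolic BP, total cholesterol level, high-density lipoprotein (HDL) level, low-density lipoprotein (LDL) level, Body Mass Index (BMI), and waist circumference". The section Primary outcomes/behavioral lists health behaviours "such as healthy diet, physical activity level, checking and monitoring BP, adherence to treatment, and predisposing factors", then "enabling factors and reinforcing factors contributing to adherence to treatment, and smoking cessation". The Outcome measures section applies the label again: "The primary outcomes of the intervention will be measured by, the researcher-made questionnaire", together with the sphygmomanometer, scale, tape and laboratory tests. No section calls any outcome secondary.

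**Sizing.** The Sample size section uses one outcome, the Hill-Bone score: means of 40 and 45, SD 10, two-tailed 5%, 80% power, 60 per group.

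**Analysis.** The Statistical methods section describes an analysis of covariance with a 95% interval for one main outcome variable, identified only as the adjusted questionnaire score. It continues: "This approach will be repeated for all the quantitative variables". Qualitative variables get chi-squared tests with no stated level.

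**Visits.** The Study setting section says that adherence, weight loss and blood pressure monitoring "will be evaluated at the primary assessment (baseline data questionnaire) and again at the 8^th^ and 24^th^ weeks". The abstract agrees, and Table 1 marks adherence and diet at week 8 as well as at close-out. The Hill-Bone section instead places that scale "at the initial and final assessments", and the diet section likewise mentions only the baseline and final questionnaires.

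**The concern.** A primary outcome is the result on which the trial agrees in advance to be judged. Here the label is given to at least 13 measures, while the sample size and the analysis section each assume there is one. The stated power and the 5% error rate belong to the Hill-Bone comparison only. A reader of the final report could not tell from this article whether a favourable result on, say, waist circumference or LDL, with no difference in adherence, meets the primary objective. The Discussion part of the abstract says that a proven impact may lead to use in the national hypertension control plan, so it matters which result counts as proof.

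The phrase about the main outcome variable does not close the gap. The Questionnaire section shows that the instrument combines Hill-Bone items with items from a WHO risk-factor questionnaire, a physical activity questionnaire and the PRECEDE constructs. A reference to its score does not by itself single out Hill-Bone.

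**Working it through.** **1. The plan's own figure.** The article gives no family-wise error rate to reproduce. Its one relevant calculation is the sample size. With difference 5, SD 10, two-sided 5% and 80% power:

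n per arm = 2 × (1.960 + 0.842)² × 10² / 5² = 62.8, so 63.

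The article states 60. At 60 per arm, power by the normal approximation is Φ(5 / (10 × √(2/60)) − 1.960) = Φ(2.739 − 1.960) = 78.2%. This small shortfall is a separate matter. What counts here is that the calculation covers one outcome and one test at 5%.

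**2. Count of outcomes labelled primary.**
- Clinical: systolic BP, diastolic BP, total cholesterol, HDL, LDL, BMI, waist = 7.
- Behavioural: diet, activity, BP monitoring, adherence, the PRECEDE factors as one, smoking = 6. With the three PRECEDE factors counted separately, 8.
- Total: 13 to 15.

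BP monitoring is scored from entries in the app, which only the intervention arm receives, so it is not clearly a between-arm test. Leaving it out gives a minimum of 12.

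**3. Chance of at least one false positive at one visit.** Assumptions: no true effect on any outcome, and each test two-sided at 5%. That level is implied by the 95% interval for ANCOVA and assumed for chi-squared.

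- Independent tests: 1 − 0.95^k.
- Equal pairwise correlation ρ: 1 − E[p(U)^k], where U is standard normal and p(u) = Φ((1.960 − √ρ·u)/√(1−ρ)) − Φ((−1.960 − √ρ·u)/√(1−ρ)).

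The documents give no correlations. The values of ρ are assumptions that show the range.

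| Tests (k) | ρ = 0 | ρ = 0.5 | ρ = 0.7 |
|---|---|---|---|
| 12 | 46.0% | 31.9% | 23.2% |
| 13 | 48.7% | 33.4% | 24.1% |
| 15 | 53.7% | 36.1% | 25.7% |

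**4. If week 8 is tested as well.** Hill-Bone and diet count once if their own sections are followed. BP monitoring is one 60-day score and counts once or not at all. The other 10 outcomes count twice:

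10 × 2 + 2 = 22 tests, or 23 with BP monitoring.

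| Tests (k) | ρ = 0 | ρ = 0.5 |
|---|---|---|
| 22 | 67.6% | 43.9% |
| 23 | 69.3% | 44.9% |

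**5. Could the design carry all 13 as primary?** Under Bonferroni the level is 0.05/13 = 0.00385, with critical value 2.891. Using the sizing inputs (a difference of half an SD) for each test:

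- n per arm = 8 × (2.891 + 0.842)² ≈ 111.4, so 112.
- Power at 60 per arm = Φ(2.739 − 2.891) = 44%.

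The trial is of a size for one primary outcome.

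**The case against.** The best reply is that the intended primary outcome can be inferred. The trial is sized on Hill-Bone, the analysis section speaks of one main variable adjusted for its baseline score, and a hierarchy or multiplicity rule may sit in an analysis plan that is not shown. Part of this stands. The absence of such a rule from an article is not a finding, and Hill-Bone is the most natural candidate. But the article never names it as primary, and three sections give the label to everything else as well.

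Several stronger readings are tempting and should not be made:

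- **A chance positive is likely.** Lipid fractions, the two blood pressures, and BMI and waist are plainly correlated. At an assumed correlation of 0.5 the single-visit figure is about one third. If only favourable results count, it is 1 − 0.975^12 = 26% to 1 − 0.975^13 = 28% even under independence. The supportable statement is that the risk is far above the nominal level.
- **There are 26 tests, with a 74% error rate.** This doubles all 13 outcomes, against the Hill-Bone and diet sections and the single 60-day monitoring score. Moreover, the Statistical methods section names no visit. Collection at weeks 8 and 24 is stated, but separate testing at each is an inference.
- **Every variable is tested in the same way at 5%.** Quantitative variables get ANCOVA and qualitative ones chi-squared, the latter with no stated level.
- **The abstract offers a rival set of primary outcomes.** It says that the most important outcomes include three, and these fall within or close to the longer lists.
- **The documents disagree about week 24.** All of them include the final assessment. They differ on whether Hill-Bone and diet are also collected at week 8.

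**Conclusion.** The point holds as an internal contradiction: 13 to 15 outcomes are labelled primary and none secondary, against a sample size for one outcome and an analysis section with one main variable that is not clearly identified. If any of these outcomes may be presented as a primary success, the single-visit chance of at least one false positive for 12 to 13 tests runs from about 23% to 49% over assumed correlations of 0.7 down to 0. Adding week 8 gives about 44% to 69% over correlations of 0.5 down to 0. The figures assume no true effects, two-sided 5% tests, equal correlations and no multiplicity rule elsewhere.

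A reader might go further and say that the trial's verdict is wholly undefined. The article does not support that, because the sizing outcome points to a de facto primary. The defect is that the text does not commit to it. It should be corrected before results are known.

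**What to change.** Name one primary outcome: the Hill-Bone total score at week 24, compared between arms by baseline-adjusted ANCOVA at two-sided 5%. This is the outcome the trial was sized on, at the end of the 6-month intervention. Make the wording agree in the abstract, Study setting, both Primary outcomes sections, Outcome measures and Statistical methods. Relabel all other outcomes, and any week 8 results, as secondary, reported with 95% confidence intervals and not as tests of trial success.

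Separately, reconcile the Hill-Bone and diet sections (initial and final assessments) with Table 1, and the Hill-Bone section also with the abstract and Study setting, on whether week 8 is included. The documents do not show which is intended.

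The cost is wording only, with no change to data collection or sample size for this point. Because the Trial status section says that recruitment has begun, the change should be dated and justified. The real price is that blood pressure, lipids and weight can no longer be claimed as primary results. If the sponsor will not accept that, the alternative is a pre-specified multiplicity procedure with a new sample size. The Bonferroni figure of 112 per arm for 13 outcomes shows the scale.
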